**Interview:**					

Mini International Neuropsychiatric Interview (MINI)	x				

Demographics	x				

Structured Clinical Interview for DSM-IV, axis II (SCID-II), section Borderline Personality Disorder	x				

Borderline Personality Disorder Severity Index-IV (BPDSI-IV)	x	x	x	x	x

(Dutch Adult Reading Test)	x				

					

**Self report measures:**					

Borderline PersonalityDisorder-47 (BPD-47)	x	x	x	x	x

Symptom Check List 90 (SCL-90)	x	x	x	x	x

European Quality of Life (EuroQol)	x	x	x	x	x

World Health Organization Quality of Life (WHOQol)	x	x	x	x	x

Young Schema Questionnaire L 2 (YSQ)	x	x	x	x	x

					

**Questionnaire for economic evaluation:**					

Cost interview	x	x	x	x	x

					

**Questionnaires for therapeutic relationship**:					

Working Alliance Inventory, patient version (WAI-P)	x	x	x	x	x

					

**Questionnaire filled in by therapists:**					

Working Alliance Inventory, therapist version (WAI-T)	x	x	x	x	x

Difficult Doctor Patient Relationship Questionnaire (DDPRQ)	x	x	x	x	x

The M.I.N.I. [32,33] will be used for assessing the Axis I diagnosis. The BPD section of the Structured Clinical Interview for the Diagnostic and Statistical Manual of Mental Disorders, Fourth Edition (DSM-IV) (SCID-II) [28,29] will be used for assessing the diagnosis BPD. If Antisocial Personality Disorder is suspected patients will not be included. To assess the severity of the borderline complaints patients will be screened using a semi structured clinical interview, the Borderline Personality Disorder Severity Index, fourth version (BPDSI-IV; range 0-90) [30,31]. A BPDSI-IV cut off score of ≥ 20 discriminates patients with BPD from patients with other personality disorders [31]. Further, if illiteracy is suspected, the Dutch Adult Reading Test [34] will be administered.

### Outcome measures

#### Primary outcome measure

The primary outcome measure is the score on the BPDSI-IV, a DSM-IV BPD criteria- based semi- structured interview: this 70- item index represents the current severity and frequency of the DSM-IV BPD manifestations. This instrument shows excellent psychometric features (Cronbach's alpha = 0.85, interrater reliability, 0.99; validity and sensitivity to change [30,31]. Previous research [30,31] found a cut-off score [35] of 15 between patients with BPD and controls, with a specificity of 0.97 and a sensitivity of 1.00.

#### Recovery criterion

The recovery criterion is, therefore, defined as achieving a BPDSI-IV score of less than 15 and maintaining this score until the last assessment.

#### Reliable change

A second criterion is reliable change [35], which reflects individual clinically significant improvement. For the BPDSI-IV, reliable change is achieved when improvement is at least 11.70 points at the last assessment [22].

#### Secondary outcome measures

##### EuroQol and WHOQol

Information on demographic factors (age, gender, marital status, education and employment status) will be collected at baseline. A secondary outcome measure is quality of life, which will be assessed by means of two widely used and psychometrically sound self-report questionnaires: the EuroQol-thermometer and EQ-5D and the World Health Organisation Quality of Life Questionnaire [36-39]. The vertical EuroQol-thermometer rating indicates one's experienced level between worst (0) and best (100) imaginable health status. The EQ-5D contains 5 dimensions: mobility, self care, daily activities, pain/discomfort and depression/anxiety. Each dimension is rated at three levels: no problems, some problems and major problems. EQ-5D health states can be converted into utility scores ranging between -0.59 and 1, with higher utility scores representing a better quality of life. The WHOQOL is a 100-item self-report questionnaire, and through the domains of physical health, psychological health, environment, personal convictions, social relationships and extent of independency, the WHO concept of quality of life is assessed.

### BPD-47, SCL-90, Young Schema Questionnaire

Other secondary outcome measures are measures for general psychopathologic dysfunction and measures of ST personality concepts, all in self-report format and with robust psychometric properties. These measures include the BPD Checklist on the burden of BPD-specific symptoms [40] and the Symptom Checklist-90 for subjective experience of general psychopathology [41,42]. A theory specific instrument is the Young Schema Questionnaire on schemas underlying Young's theory [43-46].

#### Economic evaluation

In addition to the clinical evaluation, an economic evaluation will be performed to assess the cost-effectiveness of ST with versus ST without extra phone support outside office hours. In the cost-effectiveness analysis of ST with versus ST without phone support, the difference in costs will be related to the difference in effectiveness, resulting in an Incremental Cost Effectiveness Ratio (ICER). The cost-effectiveness analysis will be based on two different effectiveness outcomes. First, cost-effectiveness will be based on the proportion of patients recovered according to the BPDSI-IV, this reflecting the investment needed to cure one patient. Secondly, cost-effectiveness will be based on Quality Adjusted Life Years (QALY), which are calculated with the EQ-5D utility scores, resulting in costs per QALY. The cost-effectiveness analysis will be based on the principles of a societal perspective using a time horizon of 18 months. Costs will be monitored by means of a cost-interview that will take place during the patient interview alongside the other measurements. The cost-interview contains items about paid and unpaid work, study, daily activities, family burden, paid help, use of healthcare and social services, use of medication, consumption of alcohol and drugs and out-of-pocket expenses. Also the number of face-to-face and telephone contacts with the study therapists will be registered.

#### Therapeutic Alliance

This study will also investigate the quality and the development of the therapeutic alliance as a mediator of change in ST. In the RCT [1] scores for the therapeutic alliance were higher in ST than in TFP. Negative ratings of therapists and patients at early treatment were predictive of dropout, while increasingly positive ratings of patient in the first half of treatment predicted subsequent clinical improvement [47]. Therapeutic alliance will be measured by the Working Alliance Inventory (WAI) and the Difficult Doctor-Patient Relationship Questionnaire - Ten Item Version (DDPRQ-10).

The WAI [48] is one of the most commonly used and extensively validated measure of the alliance. It has been found to predict therapy outcome in numerous studies [49,50]. The Dutch version of the WAI consists of three subscales of 12 items each, rated on a 5-point in stead of 7-point Likert-type scale ranging from 1 ("never") to 5 ("always"). The subscales based on Bordin's [51] working alliance theory address agreement about the goals of therapy, agreement about the tasks of therapy, and the bond between the client and therapist. Patients have to complete the patient form (WAI-P) measuring the contribution of the therapist to the alliance as perceived by the patient and therapists have to complete the therapist form (WAI-T) in which they rate the contribution of the patient to the alliance. Because of the high intercorrelations among subscales (WAI-P range: .69 - .88; WAI-T range: .67 - .89) subscale mean scores are added together to derive a global score. A higher score on the WAI indicates a higher quality of the working alliance.

Difficult Doctor-Patient Relationship Questionnaire - Ten Item Version (DDPRQ-10). The DDPRQ [52] is a self-report questionnaire, which aims to measure the extent to which patients are experienced as frustrating or difficult in the therapeutic relationship by their doctor or therapist and provoke levels of distress that transcend the expected and accepted level of difficulty. Of the DDPRQ-10 five items are about the therapist's subjective experience (e.g., "Do you find yourself secretly hoping that this patient will not return?"), four are quasi-objective questions about the patient's behavior (e.g., "How time consuming is caring for this patient?"), and one item about symptoms combines elements of the patient's behavior and the therapist's subjective response (i.e. "To what extent are you frustrated by this patient's vague complaints?"). The items are answered on a 6-point Likert-type scale ranging from 1 ("not at all") to 6 ("a great deal"). The total score of the DDPRQ equals the mean of the 10 items. A higher score indicates a higher level of therapist frustration.

#### Treatment Adherence

Treatment adherence will be monitored by means of supervision. All sessions will be audiotaped. The audiotapes will be saved for evaluation. Of all patients one audiotape between 5 and 12 months of treatment will be randomly selected. Twenty tapes will be rated by independent raters to assess the intra class correlation coefficient (ICC). The raters will be independent of the study and masked to treatment condition and outcome. The raters will be psychologists trained in ST. We will use the ST Therapy Adherence and Competence Scale for BPD [53]. This instrument consists of visual analogue scales and Likert scale items and has a competence cutoff score of at least 60.

#### Registration of the phone contact

All therapists of the condition with phone support outside office hours have to monitor the telephone contacts on standardized forms with the following specifications: duration of the contact (minutes), time (weekday/nights or weekend), point of time (day, evening, night), reason of the phone contact (crisis, therapeutic, administrative). All contacts will be registered and used for calculating the number of therapeutic and crisis contacts outside office hours. The data will also be used for another yet to publish cost-outcome article.

#### Registration of therapy sessions

Therapists have to monitor the number of sessions. The content of the sessions and the used ST-techniques have to be registered on standardized forms.

#### Problems during the implementation process

These will be monitored by the researcher, recorded in a log book, and discussed with the project group during monthly meetings and with the therapists during the monthly supervision. Possible topics that will be discussed are the experiences of therapists and research assistants with the project, no show or drop-outs of patients, support of therapists by management, peers, and crisis facilities, and organizational changes influencing the implementation process like reorganizations.

#### Implementation interventions

On the basis of explorations of possible facilitators and barriers, the following implementation interventions will be applied to enhance successful implementation [54]. Firstly, therapists, managers and assistants of different mental healthcare centers will be informed of the study. Secondly, agreements will be made with the therapists and managers about the time investment for the treatment protocol (sessions twice a week, peer supervision weekly and supervision once a month) and financial aspects. Thirdly, therapists and research assistants will be trained and support on organizational level will be offered. The process evaluation aims to assess the impact of these implementation interventions on the delivery of ST for BPD patients and to analyze the problems that may occur during the implementation process.

#### Training and supervision

As the primary aim of the study is to assess whether ST can be successfully implemented in regular mental healthcare practice, we will make the following adjustments compared to the Giesen-Bloo et al. trial. In the study of Giesen-Bloo et al. [1] the ST therapists were trained and supervised by the originator of ST, Jeffrey Young, in the implementation study the therapists will be trained and supervised by Dutch experts [55,56]. The training will be based on a structured and piloted program supported by a set of DVDs with examples of ST techniques, see Nadort et al. [54].

Therapists will be trained in a 50 hours training program (eight days during a period of two months). Essential to the treatment is expert supervision and peer supervision. During the first year monthly supervision will be provided on each site, in the second year supervision will be provided every two months. The therapists will have weekly peer supervision on each site. There will be a 1-day central supervision for all therapists once a year.

#### Frequency of sessions and treatment period

In the RCT [1] the treatment period was three years with sessions twice a week. In the implementation study there will be sessions twice a week in the first year, but sessions once a week in the second year. In the implementation study we decided to do the first evaluation after a treatment period of eighteen months. This was decided for several reasons: different treatments have shown positive results after 1-1,5 years of treatment [1,15,16,18], effectiveness already became apparent after one year [1] and most drop outs occurred during the first 1,5 years of therapy [1,15].

#### Treatment Protocol

Treatment will be offered in 45-minutes sessions twice a week in the first year and once a week in the second year. Treatment protocols address the theoretical model, treatment frame, different phases and the use of strategies and techniques [11,13,14,55-58]. Central to ST is the assumption of 5 schema modes specific for BPD. Schema modes are sets of schemas expressed in pervasive patterns of thinking, feeling and behaving [59,60]. Change is achieved through a range of behavioral, cognitive and experiential techniques that focus on (1) the therapeutic relationship, (2) daily life outside therapy and (3) past (traumatic) experiences. Recovery in ST is achieved when dysfunctional schemas no longer control or rule the patient's life.

## Sample size and Data Analysis

### Sample size

The BPDSI-IV power calculation is based on the aim of showing a difference at the patient level between the conditions with extra phone support of the therapist outside office hours versus the condition without such support. Because we do not know what the effect of the extra phone support is, it is decided to use a medium effect size of 0.5, according to Cohen [61], for the power calculation. With a minimum of 2 × 30 patients per condition, the power to demonstrate such a difference between the two conditions with two-tailed alpha of 0.05 is 84. Therefore a minimum of 60 patients is required and accordingly 30 therapists need to be recruited.

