#### Randomization

To prevent regional influences and enhance implementation TTA has to be equally spread over the different sites. Therefore a stratified randomization procedure will be used. The stratification procedure will be performed by a study-independent person and will be concealed for participating therapists, patients and researchers. Stratified per center, 50% of the therapists will be randomly allocated to the condition with extra phone support and 50% of the therapists to the condition without extra phone support. Each therapist will treat two patients either with or without phone support dependent upon the randomization. After completing the baseline assessment and signing the informed consent form patients will be randomly assigned to one of therapists of the participating institutes in their regions.

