### Strengths and limitations

Many methodological requirements for a high quality trial are met. Allocation is concealed through randomization by an external researcher. Recruitment of the patients will be done after the standard intake procedure at each site. As this study takes place within different general mental healthcare departments located in different parts of the Netherlands the results can, to a large extent, be generalized to the population of borderline patients seen in regular mental healthcare in the Netherlands. A limitation of the present study is that the assessments will be performed by research assistants who cannot remain blinded to the treatment condition of the included patients, as is always the case in trials studying the effects of psychotherapy. Nor are the patients blind to treatment condition. In this study, however, added to the main interview-based outcome measures, self-report questionnaires will be administered, that will not be influenced by the research assistants.

Another limitation is the power of this study. This implementation study is powered to demonstrate a medium or higher effect of TTA. The failure to detect any difference between conditions, does not mean that they are equivalent, only that differences, if any, will be small. A small difference however does not imply lack of clinical significance. But to detect a small effect with a significance level of .05 and a power of 80, a power analysis shows that a sample of more than 3100 patients is necessary, which is not feasible for a trial on long-lasting psychotherapy.

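### The stated 84% power for the phone-support comparison does not follow from its inputs: 30 patients per condition at d = 0.5 gives about 48% unadjusted

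*Protocol article*

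**What the plan says.** The Sample size section of the protocol article bases the calculation, with the BPDSI-IV as outcome, on "showing a difference at the patient level between the conditions with extra phone support of the therapist outside office hours versus the condition without such" help. For the effect, "it is decided to use a medium effect size of 0.5, according to Cohen [61], for the power calculation". The group size reads "With a minimum of 2 × 30 patients per condition", and the result is that "the power to demonstrate such a difference between the two conditions with two-tailed alpha of 0.05 is 84". The conclusion drawn is: "Therefore a minimum of 60 patients is required and accordingly 30 therapists need to be recruited".

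The Randomization section supplies the structure: "50% of the therapists will be randomly allocated to the condition with extra phone support and 50% of the therapists to the condition without extra" support, and "Each therapist will treat two patients either with or without phone support dependent upon the randomization".

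The Analysis section plans ANCOVA for continuous outcomes, with baseline as covariate and condition as the between-group factor. It makes a medium difference the criterion for calling the extra support definitely helpful. Under Strengths and limitations the article says "This implementation study is powered to demonstrate a medium or higher effect of TTA". It adds that a failure to find a difference does not show equivalence, but does show that any difference is small. The same paragraph says that a small effect would need more than 3100 patients at 80% power.

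**The concern.** A standardised difference of 0.5 with 30 patients per group is a familiar configuration, and its power is nearer one half than 84%. The section gives no input that would close the gap: no correlation with baseline, no averaging over follow-ups, no one-sided test.

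Two things rest on the figure. The minimum of 60 patients is derived from it. So is the planned reading of a null result, since ruling out a medium effect after a non-significant test requires high power against that effect. If power is well below 84%, phone support could be dismissed as having at most a small effect when the data do not exclude a medium one.

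**Working it through.** **Inputs.** d = 0.5, two-sided alpha 0.05, 60 patients and 30 therapists (Sample size); half the therapists per condition and two patients each (Randomization). So 30 × 2 = 60 patients in total, 15 therapists and 30 patients per condition.

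**Attempt to reproduce 84%.** For a two-sample t-test with n per group, power comes from the noncentral t distribution with df = 2n − 2 and noncentrality d·√(n/2).

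- n = 30: noncentrality = 0.5 × √15 = 1.936, df = 58, critical value 2.002. Power = **47.8%** (49.1% by the normal approximation).
- n = 60 per condition, the literal reading of the group-size phrase: noncentrality = 0.5 × √30 = 2.739. Power = **77.5%**. This would be 120 patients, against the stated 60.
- One-sided tests, contrary to the text: about 61% with 30 per condition and 86% with 60.

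None of these is 84%. The unadjusted test needs 64 per condition (128 in total) for 80% power and 71 per condition (142 in total) for 84%.

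**Planned ANCOVA.** Adjusting for a baseline with correlation r to the outcome divides the noncentrality by √(1 − r²) and costs one degree of freedom. The article gives no r, so these values are assumptions:

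| r | noncentrality | power, 30 per condition |
|---|---|---|
| 0.3 | 2.030 | 51% |
| 0.5 | 2.236 | 59% |
| 0.6 | 2.421 | 66% |
| 0.7 | 2.712 | 76% |
| 0.765 | 3.007 | 84% |

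**Detectable difference.** With 30 per condition, unadjusted, 80% power needs d of about 0.74 and 84% needs about 0.78.

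**Precision.** The unadjusted 95% confidence interval has half-width 2.002 × √(2/30) = 0.52 SD. A non-significant result can therefore accompany an observed difference as large as the medium effect itself. At r = 0.5 the half-width is about 0.52 × √0.75 = 0.45 SD.

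**The article's second power figure.** An unadjusted two-sample test at d = 0.1 with 80% power needs 2 × 2 × (1.960 + 0.842)² / 0.01 ≈ 3140 patients, which matches the figure of more than 3100. At d = 0.2 the total is 786. If instead 60 patients truly gave 84% at d = 0.5, scaling to 80% at d = 0.1 would give 60 × (0.5/0.1)² × (2.802/2.954)² ≈ 1350. The two power statements cannot come from one method.

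**Factors outside the calculation, for illustration.** With two patients per therapist the design effect is 1 + ICC. An assumed ICC of 0.05 to 0.10 lowers 47.8% to 46% to 44%. If 27% of outcomes were missing (about 22 per condition analysed), power would be 37% unadjusted and 46% at r = 0.5. The 27% is treatment dropout in the earlier three-year trial, not an estimate of missing 18-month data here.

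**The case against.** The strongest reply is that 84% is attainable with 60 patients and may come from a fuller calculation that the article condenses. The section names no test, and the BPDSI-IV is scheduled at 6, 12 and 18 months. ANCOVA on the mean of those three follow-ups, with a common correlation of 0.5, has 83.9% power. With 60 per condition, baseline ANCOVA at a correlation of 0.4 gives 84.2%, so a slip between group size and total is also a plausible origin.

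This shows that some set of assumptions reaches 84%. It does not show that the article used one. Neither the averaged endpoint nor any correlation is stated, 60 per condition conflicts with the total and with 30 therapists treating two patients each, and the figure of more than 3100 fits an unadjusted test.

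The reply does limit how far the point goes. A reader might infer that the trial is more likely than not to miss a medium effect. That is true of the unadjusted comparison, but under the planned ANCOVA, before any loss, power passes 50% once the correlation exceeds about 0.24. Nor can one say that a null result would tell us almost nothing, given power of 59% to 76% at correlations of 0.5 to 0.7. The article also already lists power as a limitation and warns against reading a null result as equivalence. What remains unsupported is its next step, that any remaining difference must be small.

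**Conclusion.** The point holds in this form: 84% does not follow from the stated inputs, which give 47.8% for an unadjusted comparison of 30 with 30. Under the planned ANCOVA the figure is about 51% to 76% for assumed correlations of 0.3 to 0.7, still short of 84%. These values assume equal groups, complete outcome data and no therapist clustering. The documents do not establish what the true power would be, because the correlation is unknown.

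Correction is needed because the sample size and the planned interpretation of a null result both depend on the number. The claim that the study is powered for a medium effect is not supported as it stands.

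**What to change.** Keep 60 patients and make these changes in the protocol article.

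1. **Sample size, power.** Replace 84 with the power under the planned ANCOVA and a named correlation (about 59% at an assumed 0.5, beside about 48% unadjusted). Alternatively, state the endpoint and correlation that yield 84%.
2. **Sample size, group size.** Change the phrase to 30 patients per condition, 60 in total.
3. **Sample size, detectable effect.** Add that 30 per condition detects d of about 0.74 at 80% power, unadjusted and before missing data and therapist clustering. Label any figure that uses 27% loss as illustrative.
4. **Strengths and limitations.** Remove "This implementation study is powered to demonstrate a medium or higher effect of TTA", and the inference that an undetected difference must be small, unless the restated power supports them. Say that a non-significant result will be read from the 95% confidence interval for the difference, against the medium effect named in the Analysis section. Put the sample size for a small effect on the same basis as the restated calculation and give the d it assumes.

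The cost is wording only: no extra patients or therapists and no change of analysis. The stated power becomes less favourable unless the assumptions behind 84% can be produced.
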